### Patient and public involvement

There was no patient or public involvement in the design and conduct of this study.

### Statistical analysis

We will use summary statistics to describe our study's contextual data (e.g., monthly admission numbers, and patterns of diagnosis). To determine if there is a change in the level of missed nursing care across periods (pre-and post-intervention), we will use linear regression analysis with the NCI as the outcome variable and observation period as the main independent variable. Linear regression will also be used to assess the effect of intervention after adjusting for potential confounders such as patient severity category, and observation made on a weekend/weekday. We will report the risk ratios and corresponding 95% confidence intervals. For our secondary objectives, we will use interrupted time series analysis to track changes in the secondary quality indicators.

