#### Statistical power

Drawing on prior experience for our primary outcome [17], assuming a 5% improvement in mean NCI scores (SD- 15%), adjusting for clustering with a design effect of 1.5 and setting α and β at 5% and 80% respectively, the minimum sample size for this study will be 213 in each period (pre-intervention and post-intervention). This will be split equally across the 4 hospitals (55 babies in each hospital per period). This will further be split across randomly sampled 12-h weekday and weekend shifts and across illness severity categories (A, B, C) (Fig. 3). In each shift, we will aim to observe 4 co-located babies for the entire duration of the randomly sampled 12-h blocks. This has been deemed logistically feasible based on prior experience using the NCI tool within the same setting [17].

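### The sample size allows for clustering with a design effect of 1.5, but the stated primary model makes no allowance for it; the type I error could reach about 11%

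*Protocol article*

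**What the plan says.** The Statistical power section of the protocol article starts from a 5-point improvement in mean NCI and an SD of 15, "adjusting for clustering with a design effect of 1.5", and arrives at 213 babies in each period. On allocation it says: "This will be split equally across the 4 hospitals (55 babies in each hospital per period"). On sampling it says: "In each shift, we will aim to observe 4 co-located babies for the entire duration of the randomly sampled 12-h blocks".

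The Study design section makes the within-site comparison of before with after the primary analysis. The Statistical analysis section then gives the model: "we will use linear regression analysis with the NCI as the outcome variable and observation period as the main independent variable". A second, adjusted linear regression follows, with severity category and weekend or weekday as examples of covariates. Neither model has a hospital or shift term, a random effect, generalised estimating equations or a cluster-robust variance, and nothing elsewhere in the article supplies one. The article does not say which level of clustering the 1.5 describes.

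**The concern.** The two sections treat the same data differently. The sample size section takes the babies to be correlated and pays for that with 71 extra babies per period (213 − 142). The analysis section names a regression that, without further qualification, takes them to be independent.

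The sampling scheme makes correlation likely. Four babies in one place are watched over the same 12 hours, under the same nurses and the same workload. Period is constant within a shift, so correlation within shifts does not cancel from the before-after contrast.

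At stake are the error rate and interval coverage of the study's main hypothesis test. The estimated mean difference is not biased by this; its stated precision may be.

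**Working it through.** **Inputs (Statistical power section).** Difference 5, SD 15, alpha 5%, power 80% (the text labels this β), design effect 1.5, 213 per period, 4 hospitals with 55 babies each per period, 4 babies per shift. Sidedness is not stated. Two-sided is assumed because it reproduces the plan's figure; one-sided gives 168.

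**1. The plan's own figure.** n = 2 × (1.96 + 0.8416)² × 15² / 5² = 141.3, rounded up to 142. Then 142 × 1.5 = 213, an exact match.

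**2. What 1.5 means at each level, if one level carries all of it.**
- Shifts of 4: ICC = 0.5 / 3 = 0.167.
- Hospital-periods of 55: ICC = 0.5 / 54 = 0.009.

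**3. Effect of ignoring it.** If the 1.5 is correlation nested within period, the true standard error is √1.5 = 1.225 times the one reported.
- Type I error: 2 × [1 − Φ(1.96 / 1.225)] = 2 × [1 − Φ(1.600)] = 0.110. Coverage of the nominal 95% interval is about 89%.
- Half-width at 213 per period, clustering ignored: 1.96 × 15 × √(2/213) = 2.85 NCI points.
- Half-width with clustering: 2.85 × 1.225 = 3.49 points. The reported interval is 18% too narrow (1 − 1/1.225).
- Power at 213 per period is 80.2% with the design effect applied. A model that ignores clustering implies 93.1%.

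**4. Simulation under no period effect.** Four hospitals, 2 periods, 14 shifts per hospital-period (55 / 4 = 13.75, rounded up), 4 babies per shift; 4,000 runs per scenario.

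| Source of correlation | Regression on period alone | With hospital fixed effects |
|---|---|---|
| None | 5.2% | 5.7% |
| Shift, ICC 0.167 | 9.9% | 11.3% |
| Hospital-by-period, ICC 0.009 | 11.4% | 11.3% |
| Stable hospital effect only, ICC 0.10 | 4.1% | 5.1% |

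A separate run of 6,000 gave 10.8% for the shift scenario with regression on period alone, and 5.1% when shift means were analysed with hospital fixed effects. So hospital terms alone do not cure shift clustering; a shift-level allowance does.

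**5. If part of the shift variance is shift type.** The Observations of care section stratifies shifts by day or night and weekday or weekend. If both periods follow the same scheme, variance due to shift type cancels from the contrast. With a total shift ICC of 0.167 and the remaining 0.833 within shifts:
- Half of it shift type (assumption): variance ratio 0.833 + 4 × 0.0833 = 1.167; type I error 2 × [1 − Φ(1.96 / √1.167)], about 7%.
- A quarter shift type (assumption): variance ratio 0.833 + 4 × 0.125 = 1.333; type I error about 9%.

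**The case against.** The strongest reply is that the article says only linear regression. It does not say ordinary least squares and does not exclude a clustered variance; the covariate list is illustrative, and a fuller analysis plan may settle the variance estimator. That is fair as far as it goes: independence is inferred from silence. But the article does fix the outcome, the model and its main regressor, and an unqualified linear regression does not account for the correlation that the same article assumes. Followed as written, it gives wrong standard errors under that assumption.

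The second reply is about direction, and it stands. All four hospitals contribute equally to both periods, so a stable hospital effect cancels from the period contrast, and ignoring it is slightly conservative (about 4% in the simulation). A reader might infer that the intervals must be too narrow whatever the 1.5 stands for. The article does not support that, because it does not name the level. Balanced shift types also reduce the inflation.

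Three further inferences should be resisted.
- That the 1.5 covers one level and leaves nothing for the other. A single multiplier can cover both: a shift component of 0.08 and a hospital-period component of 0.005 give 1 + 3 × 0.08 + 54 × 0.005 = 1.51. The ICCs in step 2 are the extremes.
- That the error rate is really 17–20%, or the power about 49%. The first adds hospital-by-period ICCs of 0.01–0.02 that have no source in the article. The second belongs to a test on four hospital differences that the plan does not propose.
- That the shift identifier is already recorded. The article describes shift-level workload data but does not state this, and the checklist is not shown.

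**Conclusion.** The concern holds in a conditional form. The article sizes the study for correlated observations and names a primary model with no allowance for them. If the 1.5 reflects correlation within shifts or hospital-by-period variation, the nominal 5% test has a type I error of up to about 11%, and the 95% half-width is understated at 2.85 instead of 3.49 NCI points.

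The upper figure assumes a two-sided test, the plan's design effect taken at face value, and none of the shift variance explained by shift type balanced across periods. The inflation falls to about 7–9% if a half to a quarter of the shift variance is of that kind. There is none if the 1.5 reflects only stable hospital differences. Observing four co-located babies per shift makes some correlation within shifts the natural expectation, so the mismatch should be resolved before analysis.

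**What to change.** In the Statistical analysis section, specify one of these for the primary comparison:
- a linear mixed model for NCI with period and hospital as fixed effects and a random intercept for shift (about 4 × 2 × 14 = 112 shifts), with a small-sample degrees-of-freedom correction; or
- linear regression with hospital fixed effects and standard errors clustered on shift.

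Clustering the standard errors on the four hospitals alone would be unreliable without a small-sample correction.

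In addition:
- ensure that a shift identifier is kept in the analysis data;
- state in the Statistical power section which cluster level or levels the 1.5 represents;
- report the four within-hospital differences as a sensitivity analysis. Neither model above contains a hospital-by-period term, and this shows whether the change is consistent across sites.

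The cost is wording and one data field. The sample size stays at 213 per period. If the 1.5 is right, intervals become about 22% wider than under the stated model, which 213 already allows for.

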### Objectives

#### Primary objective

To determine the effect of enhancing nurse staffing on missed nursing care measured using the nursing care index (NCI) tool in a before and after design study of four hospitals.

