#### Primary and secondary objective (how supplemental nurse staffing impacts the level of missed nursing care)

Using bedside observations of care, we will employ a before and after design in 4 intervention hospitals selected from the 12 NEST360 hospitals. Our baseline observations will be conducted in the 4 intervention hospitals before enhancing nurse staffing and additional observations will be performed after 6 months. At the same post-intervention time point observations will be made in a further set of 4 hospitals from the original 12 that have not received the workforce intervention (Fig. 1). Our primary analysis will be the before-and-after within-site comparison, the single time-point observations in the 4 non-intervention sites will serve as an external reference for our 4 intervention hospitals. Data on nurse staffing metrics will be collected for 6 months before the workforce enhancement and in the 6 months leading to the post-intervention assessment in the 4 intervention hospitals. These data will be used to assess whether and to what degree providing additional nurses changes nurse staffing metrics as an indication of intervention fidelity. Similar data on nurse staffing metrics will be collected from the 4 reference hospitals and then data from all 8 hospitals at the post-intervention time point will be used to address our secondary objective of exploring the relationship between nurse staffing metrics and nurse-delivered care.

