#### Data collection tool

##### Missed nursing care data collection tool

To measure the level of missed nursing care before and after our intervention (our primary objective), we will employ an adapted version of the Nursing Care Index (NCI) tool [17] (Additional file 1). This tool involves performing non-participatory observations of nursing care provided to newborns using a structured checklist (supplementary material). Our adaptation to the existing tool includes key data on potential confounders of the relationship between nurse staffing and missed nursing care, for example, proxy data to estimate nursing workload on shifts (number of high acuity babies, babies on interventions such as Continuous Positive Airway Pressure), support staff available on shift, and presence of the necessary medical equipment for carrying out certain nursing duties such as pulse oximetry recordings. We will pilot our adaptation of the NCI tool for feasibility.

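### The primary before-after effect should be decided by the model adjusted for the sampling factors; the plan leans towards a period-led model, which is the weaker of its two regressions

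*Protocol article*

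**What the plan says.** The primary objective is "To determine the effect of enhancing nurse staffing on missed nursing care measured using the nursing care index (NCI) tool". The Study design section fixes the contrast: "Our primary analysis will be the before-and-after within-site comparison". It names no model and no covariates.

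The Statistical analysis section then describes two regressions for that contrast. In the first, used to establish whether missed care changed, "we will use linear regression analysis with the NCI as the outcome variable and observation period as the main independent variable". The second follows: "Linear regression will also be used to assess the effect of intervention after adjusting for potential confounders such as patient severity category", with weekend or weekday observation as the other example.

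The section on the data collection tool lists further candidates: "Our adaptation to the existing tool includes key data on potential confounders of the relationship between nurse staffing and missed nursing care". Its examples are workload proxies, support staff and equipment.

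The sampling is stratified. Observations of care aims for equal numbers of day and night shifts, a 5:3 weekday to weekend ratio, and babies of different severity. Statistical power sets 55 babies per hospital per period and splits them across shifts and severity categories A, B and C.

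**The concern.** The protocol itself says that missed care varies with illness severity and with shift timing, and it samples by those factors. A model containing period alone ignores them, which is a weakness under either way of running the sampling.

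- **Strata held to quota in both periods.** The period estimate is balanced, but the error term still contains the variation between strata. The reported standard error is too large and the test loses power.
- **Mix free to differ between periods.** The period coefficient then includes any shift in case mix or shift mix. In a non-randomised before-after study that is confounding. The two models can also give different answers, and if a significant result from either could be claimed, the error rate would exceed 5%.

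The within-site contrast named as primary also sits more naturally with a model that contains hospital.

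**Working it through.** **The plan's own figure.** Inputs from Statistical power: difference 5, SD 15, "setting α and β at 5% and 80% respectively" (the 80% read as power), design effect 1.5. n = 2 × (15 × (1.960 + 0.842) / 5)² = 141.3, so 142 per period, and 142 × 1.5 = 213. This matches the stated 213. A one-sided test would give 112 × 1.5 = 168, so two-sided 5% is implied. The calculation has no covariate adjustment. Recruitment of 4 × 55 gives 220 per period.

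**Assumptions.** The share of NCI variance explained by the sampling factors, R², is not given; I use 10, 20 and 40%. SD is 15, there are 220 babies per period, and clustering is ignored at first.

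Let SE = 15 × √(2/220) = 1.430 and k = √(1 − R²) = 0.949, 0.894, 0.775. Φ is the normal distribution function.

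**Case 1: strata fixed by quota.** Both models give the same period estimate, with true standard error k × 1.430, but the period-only model reports 1.430.

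- False-positive rate, period-only: 2 × Φ(−1.96/k), with 1.96/k = 2.066, 2.191, 2.530.
- Power at 3 points (3/1.430 = 2.098): period-only Φ((2.098 − 1.96)/k); adjusted Φ(2.098/k − 1.96).
- Power at 5 points (5/1.430 = 3.496): the same formulas with 3.496.
- The adjusted test is significant whenever the period-only test is, so disagreement is the difference in power.

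| R² | False positive, period-only | Power at 3 points: period-only / adjusted | Power at 5 points: period-only / adjusted | Disagree at 5 points |
|---|---|---|---|---|
| 10% | 3.9% | 56% / 60% | 94.7% / 95.8% | about 1% |
| 20% | 2.8% | 56% / 65% | 95.7% / 97.4% | about 2% |
| 40% | 1.1% | 57% / 77% | 97.6% / 99.5% | about 2% |

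In this case the chance that at least one model is falsely significant stays at 5%.

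**Case 2: mix free to vary by chance.** Each test is valid alone. The two z-statistics have correlation k, with means d/1.430 and d/(1.430k) for a true difference d. From the bivariate normal distribution:

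| R² | At least one falsely significant | Disagree at 3 points | Disagree at 5 points |
|---|---|---|---|
| 10% | 6.5% | 11% | 3.2% |
| 20% | 7.1% | 16% | 4.4% |
| 40% | 8.0% | 27% | 5.9% |

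Simulation with a three-level severity covariate agrees with both tables within simulation error.

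**Clustering.** Dividing by the plan's design effect gives 220/1.5 = 146.7 and SE = 1.752. Disagreement at 5 points rises to 2.6, 5.0 and 8.2% under quota, and to 7.1, 10.5 and 15.5% with a free mix.

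**Which case applies.** Hospital is fixed by quota (55 per hospital per period), and the shift targets are stated. The text available gives no ratio for severity, and Figure 3 is not shown. The description is closer to Case 1, but Case 2 cannot be excluded for severity.

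**The case against.** A reader might infer that the two regressions are co-equal and that the sponsor may claim whichever is significant. The documents do not support that. Nothing says either result may be claimed, and the wording leans towards the first model: it comes first, it tracks the primary outcome (a change in NCI), the second is introduced as an addition, and the sample size is an unadjusted comparison of two means. Nor are the missing ranking and the open covariate list faults in themselves. This is a journal article, and a full protocol or analysis plan that is not shown may supply both.

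Three further points stand. Period is called the main independent variable, not the only one, so a period-only first model is the likely reading but not a certain one. Under quotas, which the sampling description suggests, there is no either-model inflation. The 3-point difference is illustrative; the plan is built on 5 points, where disagreement is much rarer. Reporting crude and adjusted estimates side by side is also ordinary practice in a before-after study.

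None of this argues for letting a period-only model lead. In both sampling cases the adjusted model is at least as good, and it uses factors the study already records.

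**Conclusion.** The point holds as a recommendation on the choice of deciding model, not as a charge that the result can be read either way. For a stratified, non-randomised before-after comparison, the model adjusted for the sampling factors should answer the primary objective.

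The gain is modest at the planned effect. Ignoring clustering, the models disagree in about 1 to 2% of studies under quota and 3 to 6% with a free mix; the plan's design effect of 1.5 raises these ranges. The gain is larger for a smaller true effect: at 3 points the period-only test has about 56% power against 60 to 77% adjusted. All of this rests on an assumed R² of 10 to 40%. Protection against a shift in case mix is a further benefit, which the documents give no figures to quantify. Adjustment does not remove a change over time unrelated to staffing.

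**What to change.** In Statistical analysis, state: the primary objective is answered by the period coefficient (difference in mean NCI with its 95% confidence interval) from a linear model adjusted for hospital, day or night shift, weekday or weekend, and severity category. The period-only model, and any model adding the workload, support-staff or equipment variables, is supportive and cannot replace it. If an analysis plan already names a deciding model, bring the two texts into line.

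The cost is two sentences. No new data are needed and the 213 per period is unchanged. The adjustment uses 3 + 1 + 1 + 2 = 7 degrees of freedom out of 440 observations. The downside is that a favourable unadjusted result cannot be claimed if the adjusted one is not significant.

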### Site selection and eligibility criteria

We have selected solely public district-level health facilities that are part of the CIN and that have received a standard set of neonatal equipment and linked technical training as part of the NEST360 programme as study sites. Previous research has shown that these types of public hospitals experience the greatest level of missed nursing care associated with poor staffing levels [17]. Intervention sites are selected to be within 1 to 3 h of the Kenyan Capital, Nairobi because of travel restrictions linked to the Covid-19 pandemic enabling feasible access to these research sites. Table 1 provides a comparison of the staffing numbers and average admissions for the 4 intervention sites.

**Table 1 Tab1:** Bed capacity, annual admissions, and staffing strengths across the 4 intervention hospitals

Metric	Hospital A	Hospital B	Hospital C	Hospital D
Newborn unit bed capacity^a^	53	50	38	47
Nurse staffing numbers (pre-intervention)	17	11	10	8
Expected percentage change in nurse staffing after adding 3 extra nurses (%)	17.6	27.3	30.0	37.5

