#### Observations of care

We will employ four observers across our 4 intervention sites to conduct bedside observations of care. These will be staff with a qualification in Allied Health Sciences, for example, nutrition science as proved successful in prior work [17]. We will avoid employing nurses or medical doctors as this group are likely to ascribe their professional standards to the care they are observing, and it would be challenging for them to retain non-participant status.

Because missed nursing care has previously been shown to vary across shift timing (day and night, weekday and weekend) and also patient severity [17], we will employ stratified data collection with the aim to equally distribute observations across the morning and night shifts and in a 5: 3 ratio across weekdays and weekends. This is carried out to maximise variation in the observational periods and to have a representative estimate of missed care across all shifts. Our stratified data collection will also involve conducting observations on babies with different illness severities (Fig. 3).

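### The primary before-and-after regression does not name hospital or day/night, two of its own sampling strata; this costs precision and leaves the estimate open to drift in the achieved mix

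*Protocol article*

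**What the plan says.** Under Study design, in the part on the primary and secondary objective: "Our primary analysis will be the before-and-after within-site comparison". The four non-intervention hospitals serve only as an external reference.

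Sampling is structured to match. Statistical power fixes the hospital split: "This will be split equally across the 4 hospitals (55 babies in each hospital per period". Observations of care gives the reason for stratifying by shift: "Because missed nursing care has previously been shown to vary across shift timing (day and night, weekday and weekend) and also patient severity". It then aims to "equally distribute observations across the morning and night shifts", with a 5:3 weekday/weekend ratio and a spread over severity categories.

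Statistical analysis says "we will use linear regression analysis with the NCI as the outcome variable and observation period as the main independent variable". It then describes a second regression "after adjusting for potential confounders such as patient severity category, and observation made on a weekend/weekday". No hospital term, stratification by hospital or day/night term is named in either.

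The section on the data collection tool adds that the adapted checklist records "key data on potential confounders of the relationship between nurse staffing and missed nursing care", including proxies for shift workload.

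**The concern.** The sampling is controlled on four factors: hospital, day/night, weekday/weekend and severity. The analysis names the last two. A regression of NCI on period without hospital compares all pre-period babies with all post-period babies, which is a pooled comparison rather than the within-site one that the design section declares.

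Two things are at stake. First, any NCI difference between hospitals, or between day and night, stays in the residual. The reported interval is then wider than the design warrants, and much of the benefit of stratified sampling is lost. Second, the pooled estimate has no protection if the achieved mix of hospitals or shifts differs between the two periods.

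Table 1 makes site differences plausible. The four units have 17, 11, 10 and 8 nurses for 53, 50, 38 and 47 beds, or about 3.1, 4.5, 3.8 and 5.9 beds per nurse. They differ in the very factor that the hypothesis links to missed care.

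**Working it through.** **1. The plan's own figure.** Inputs from Statistical power: difference 5 points, SD 15, α 5% (two-sided assumed), power 80%, design effect 1.5. Per period, n = 2 × 15² × (1.960 + 0.842)² / 5² = 141.3, rounded up to 142; 142 × 1.5 = 213. This matches the protocol exactly (a one-sided test would give 168). The planned number is 4 × 55 = 220 per period.

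**2. Precision without the two terms.** SE = 15 × √(1.5 × 2/220) = 1.75. Power = Φ(5/1.75 − 1.96) = 81.4%.

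**3. Precision with them.** Let R² be the share of NCI variance that lies between hospitals and between day and night. The documents do not give it, so it is assumed. With the design effect held at 1.5, SE = 1.75 × √(1 − R²).

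| Assumed R² | SE | Power |
|---|---|---|
| 0 | 1.75 | 81.4% |
| 0.05 | 1.71 | 83.4% |
| 0.10 | 1.66 | 85.3% |
| 0.20 | 1.57 | 89.1% |

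**4. Check by simulation under exact balance.** Each run had 4 hospitals × 14 shifts × 4 babies per period, with day and night equal, a true effect of 5 and a total SD of 15. The shift ICC was 0.167, which is what a design effect of 1.5 implies with 4 babies per shift: (1.5 − 1)/(4 − 1). There were 600 runs per scenario, with standard errors clustered by shift.

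| Assumed site SD; day/night difference | Share of variance | Estimated SE without / with the terms | Actual SD of the estimate, either model | Power without / with |
|---|---|---|---|---|
| 0; 0 | 0 | 1.72 / 1.70 | 1.71 | 84% / 84% |
| 5; 5 | (25 + 6.25)/225 = 13.9% | 1.91 / 1.58 | 1.66 | 77% / 88% |
| 7.5; 5 | (56.25 + 6.25)/225 = 27.8% | 2.10 / 1.45 | 1.48 | 70% / 93% |

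A hand check of the middle row: the variance left after site and day/night is 225 − 31.25 = 193.75, of which 0.167 × 193.75 = 32.4 is between shifts and 161.4 between babies. Without the terms, SE ≈ √[2 × ((31.25 + 32.4)/56 + 161.4/224)] = 1.93. With them, SE ≈ √[2 × (32.4/56 + 161.4/224)] = 1.61. Both agree with the simulation.

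The loss is larger here than in step 3 because site and day/night differences are shared by all four babies in a shift, so a shift-clustered standard error counts them in full. Under balance the point estimate and its true variability are the same in both models. What is lost is the accuracy of the reported standard error, and with it power.

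In the same middle scenario the unclustered least-squares SE was 1.41 without the terms and 1.31 with them, both below the actual 1.66. Adding the terms without allowing for shift would therefore widen that understatement.

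**5. Bias.** Bias = Σ (post share − pre share) × stratum mean.
- Quotas met: every share is equal in both periods, so the bias is 0.
- Hospital counts drifting from 60/57/53/50 to 50/53/57/60: with evenly spaced site means and SD 5 (means −6.71, −2.24, 2.24, 6.71), bias = (2 × 10 × 6.71 + 2 × 4 × 2.24)/220 = 0.7 points. The range is 0.4 to 1.0 for site SD 3 to 7.5.
- Counts drifting from 65/58/52/45 to 45/52/58/65: 0.8 to 2.0 points over the same range of site SD.
- The share of one shift type moving from 50% to 60%: 0.10 × 5 = 0.5 to 0.10 × 10 = 1.0 points for day/night differences of 5 to 10.

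These compare with a target of 5 points. Every drift, site SD and day/night difference here is an assumption.

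**The case against.** Several objections carry weight.

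- **The covariate list is illustrative.** Severity and weekday/weekend are given as examples, and this is a condensed article whose analysis plan is not shown. A reader might infer that hospital and day/night are excluded; the text supports only that they are not named. That stands. But the first model, on period alone, is not open-ended, and the article's examples take up two of the design's four strata and pass over the one that would make the comparison within-site.
- **Within-site may describe the design.** The sentence can be read as the same hospitals before and after, as opposed to intervention against reference hospitals. That is a fair reading and softens the contradiction. It does not remove the reason to condition on hospital.
- **The quotas deal with confounding by mix.** A reader might infer that the intervention effect is biased by site or shift mix. The documents do not support this: equal numbers per hospital per period and equal day and night sampling make both factors orthogonal to period, and step 5 gives zero bias. What remains is conditional. The day/night split is stated as an aim, and each observation depends on consent from a parent and from the nurse on duty, so drift is possible but not shown.
- **The sizes are assumed.** True. The documents contain no between-hospital variance and no day/night difference, and with neither there is nothing to gain.
- **Workload is not an established omission.** A reader might infer from the tool section that census or acuity belongs in the primary model. Nothing commits these variables to it, and their description closely matches the secondary objective. Adjustment is also debatable, because added nurses could change census and acuity: the protocol itself places mortality downstream of staffing.

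**Conclusion.** The point holds as a matter of precision and clear specification. The stated regressions name neither hospital nor day/night, although the primary analysis is declared within-site and both factors structure the sampling. With the quotas met, the estimate is not biased by site or day/night mix. The estimated standard error is inflated and power is lost to the extent that sites or shifts differ in NCI: 1.75 against 1.71 to 1.57, and about 81% against 83–89%, for an assumed 5% to 20% of variance explained and a design effect held at 1.5. The simulated loss is larger when clustering by shift is modelled directly. With no site or shift differences the models are equivalent.

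Bias arises only if the achieved mix changes between periods. In the illustrated drifts it is 0.4 to 2.0 points for hospital and 0.5 to 1.0 for day/night. This is worth correcting because it is nearly free. It does not invalidate the design or the sample size.

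**What to change.** State the primary model in full: NCI on period, hospital (fixed effect), severity category, weekday/weekend and day/night, with standard errors that allow for clustering of babies within shift. The strata and the clustering should go in together, for the reason shown in step 4.

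Keep any adjustment for patient census or number of high-acuity babies as a prespecified sensitivity analysis only, because the intervention could affect both. Do not adjust the primary model for nursing hours: the section on intervention fidelity treats the staffing metrics as mediators.

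The cost is a sentence or two of wording. Hospital and shift type are known for every observation by design, so no new data are needed. The added terms use 3 (hospital) + 1 (day/night) = 4 degrees of freedom, out of about 440 babies (2 × 220) observed on roughly 112 shifts (4 hospitals × 2 periods × 14). The sample size of 213 per period does not change.
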